## Supplementary Materials

**Table 1.** Baseline patient characteristics.

|                                                            |                   |
|------------------------------------------------------------|-------------------|
|                                                            | N=73              |
| Age (years)                                         | 68, (range 42-90) |
|                                                            |                   |
| Gender                                              |                   |
| Male                                                       | 31 (42%)          |
| Female                                                     | 42 (58%)          |
|                                                            |                   |
| Race                                                |                   |
| American Indian/Alaskan Native                             | 2 (2.7%)          |
| Asian                                                      | 1 (1.4%)          |
| Black/African American                                     | 2 (2.7%)          |
| Pacific Islander                                           | 1 (1.4%)          |
| Unknown                                                    | 7 (9.5%)          |
| White/Caucasian                                            | 60 (82.2%)        |
|                                                            |                   |
| Eastern Cooperative Group (ECOG) Performance Status |                   |
| 0                                                          | 9 (12%)           |
| 1                                                          | 42 (58%)          |
| 2                                                          | 14 (19%)          |
| 3                                                          | 7 (9.6%)          |
| 4                                                          | 1 (1.4%)          |
|                                                            |                   |
| Primary Tumor Origin                                |                   |
| Bladder                                                    | 1 (1.4%)          |
| Breast                                                     | 10 (14%)          |
| Colorectal                                                 | 3 (4.1%)          |
| Gastroesophageal                                           | 3 (4.1%)          |
| Gynecologic                                                | 3 (4.1%)          |
| Head & neck                                                | 2 (2.7%)          |
| Renal                                                      | 4 (5.5%)          |
| Non-small cell lung cancer                                 | 37 (51%)          |
| Sarcoma                                                    | 3 (4.1%)          |
| Melanoma                                                   | 3 (4.1%)          |
| Skin (non-melanoma)                                        | 3 (4.1%)          |
| Unknown primary                                            | 1 (1.4%)          |

**Table 2.** Protocol-related Common Terminology Criteria for Adverse Events version 4 toxicities.

| Grade 1   |        | Grade 2  |       |
|-----------|--------|----------|-------|
| Alopecia  | N = 18 | Alopecia | N = 3 |
| Dizziness | N = 1  | Fatigue  | N = 4 |
| Fatigue   | N = 4  | Headache | N = 1 |
| Headache  | N = 2  | Nausea   | N = 1 |
| Nausea    | N = 1  |          |       |

**Table 3.** Protocol FFSRT dose constraints. Dmax, maximum dose; cc, cubic centimeter.

| Organ at Risk | 27 Gy in 3 fractions
(GTV < 3 cm) | 30 Gy in 5 fraction
(GTV 3.0-4.0 cm) |
|---------------|--------------------------------------|-----------------------------------------|
| Brainstem     | Dmax < 16 Gy, 1 cc < 12 Gy           | Dmax < 22 Gy, 1 cc < 20 Gy              |
| Optic Nerves  | Dmax < 16 Gy, 1 cc < 12 Gy           | Dmax < 22 Gy, 1 cc < 20 Gy              |
| Optic Chiasm  | Dmax < 16 Gy, 1 cc < 12 Gy           | Dmax < 22 Gy, 1 cc < 20 Gy              |
| Brain         | Mean < 8 Gy                          | Mean < 8 Gy                             |

## **1.0 Objectives**

### **Primary Objectives**

1. To assess the efficacy and safety of frameless fractionated stereotactic radiation therapy (FFSRT) on the treatment of solitary and oligometastatic brain metastases in the MD Anderson Houston [name] Anderson Radiation Treatment Centers in [name] Anderson affiliates and the main campus of MD Anderson, for patients unable or unwilling to undergo frame-based stereotactic radiosurgery (SRS).

### **Secondary Objectives**

1. To assess 6-month local control, intracranial progression-free survival and overall survival.
2. To collect data on charges and reimbursements of patients treated with FFSRT to compare those charges and reimbursements if the same patients had been treated with single-fraction, frame-based Gamma Knife SRS.

## **2.0 Rationale**

Solitary and oligometastatic brain disease has been effectively managed with frame-based SRS in a single fraction with Gamma Knife, Cyber Knife or linac-based treatment delivery. (1) However, there are published data to suggest that similar local control and toxicity profiles can be achieved with FFSRT. (2,3,4,5) If, in fact, FFSRT is as effective and safe as frame-based single fraction SRS, then more patients would have access to the therapy, since 1) a neurosurgical procedure with frame would not be necessary, and 2) the equipment necessary for FFSRT is more readily available at radiation oncology facilities. In the setting of health care cost containment, if FFSRT is proven to be as effective as frame-based, single-fraction SRS, it would not be necessary to purchase the additional equipment otherwise needed for centers to offer the frame-based treatment for patients with oligometastatic brain disease. In the setting of the MD Anderson Regional Care Centers, currently only The Woodlands center offers frame-based SRS. Therefore, all patients eligible for focal treatment for their oligometastatic disease must be referred either to the Texas Medical Center or to The Woodlands facility. The additional travel, time and expense may be a burden for patients, who often have limited life expectancy.

## **3.0 Type of Subjects to be Studied**

All patients with 1-4 metastatic brain lesions who are considered eligible for single-fraction, frame-based SRS, who are unable or unwilling to undergo frame-based SRS.

### **Eligibility**

Patients and/or their disease must fulfill the following criteria to be enrolled in this prospective study:

1. Greater than or equal to 18 years of age.

2. One to 4 untreated metastatic brain lesions.
3. Each brain lesion must be less than or equal to 5 cm in diameter and not an optimal surgical candidate.
4. Patient must be able have an MRI of the brain for treatment planning.
5. Histologic confirmation of malignancy.
6. For patients of childbearing potential, non-pregnant state, confirmed by negative serum or urine beta-HCG within (7) days of planned radiation treatment.
7. GFR adequate for IV contrast delivery for imaging.
8. No concurrent chemotherapy.
9. Patient may have had prior therapy for brain metastasis, including radiosurgery and surgical resection at the discretion of the treating physician however only new untreated lesions will be followed on protocol.

### **Ineligibility**

Patients and/or their disease meeting any of the following criteria are ineligible for enrollment.

1. Less than 18 years old.
2. Five or more metastatic brain lesions.
3. Brain lesion(s) greater than 5 cm in diameter.
4. Lesion(s) involving the brainstem, optic chiasm or optic nerve(s).
5. Patients unable to have IV contrast for CT and MRI imaging.
6. Patient unable to have an MRI of the brain.
7. Patients willing to be treated with frame-based Gamma Knife SRS at MD Anderson main campus or MD Anderson at The Woodlands.
8. Positive pregnant status confirmed by serum or urine pregnancy test.
9. Primary small cell lung cancer, myeloma, lymphoma, leukemia, or other histologies not optimally treated with SRS.
10. Patients currently receiving chemotherapy/biologic/immunotherapy as these need to be held during FFSRT
11. Prior whole brain radiotherapy or conventional external beam radiotherapy.

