## 7.0 Procedure to Obtain Informed Consent

If the treatment recommended for a patient with a solitary or oligometastatic brain lesion(s) is single-fraction frame-based Gamma Knife SRS, the patient will be offered referral to the main campus of MD Anderson or MD Anderson at The Woodlands. If the patient is unable or unwilling to be treated at one of those facilities, likely due to distance or the use of an invasive head frame for treatment, then enrollment on this prospective database study will be offered. The treating radiation oncologist will obtain consent for study participation from the patient. Written informed consent will be obtained on all participants.

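### Exclusion 7 tests willingness alone, so patients who would accept Gamma Knife at the two named sites but cannot have it are ineligible, contrary to sections 1.0, 3.0 and 7.0

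*Protocol*

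**What the plan says.** Three places in the protocol describe who the study is for, and each gives two alternatives joined by "or".

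- Section 1.0, Primary Objectives: the treatment is assessed "for patients unable or unwilling to undergo frame-based stereotactic radiosurgery (SRS").
- Section 3.0, opening statement: patients with 1 to 4 brain lesions "who are considered eligible for single-fraction, frame-based SRS, who are unable or unwilling to undergo frame-based SRS".
- Section 7.0, consent procedure: a patient for whom Gamma Knife SRS is recommended is first offered referral to the main campus or The Woodlands. Enrolment is then offered on this condition: "If the patient is unable or unwilling to be treated at one of those facilities, likely due to distance" or because of the head frame.

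The Ineligibility list under section 3.0 opens with "Patients and/or their disease meeting any of the following criteria are ineligible for enrollment", so one criterion is enough to bar a patient. Item 7 of that list reads "Patients willing to be treated with frame-based Gamma Knife SRS at MD Anderson main campus or MD Anderson at The Woodlands". It does not mention ability. No item in the Eligibility list mentions ability or willingness to have frame-based SRS either.

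**The concern.** Item 7 should be the mirror image of the target population. If patients who are unable or unwilling are to be enrolled, those to be kept out are the ones who are able and willing. Item 7 keeps out everyone who is willing to be treated at the two sites, whether or not they are able. It therefore negates only one of the two alternatives.

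What is at stake is consistent application of an enrolment rule. The study runs at several centers (section 1.0). A screener working from the numbered list would refuse a willing-but-unable patient. A radiation oncologist working from section 7.0 would enrol the same patient, who would then carry a nominal eligibility deviation. The enrolled population would depend on which page a site followed. The affected patients are also one of the two groups named in the primary objective, and section 2.0 justifies the trial partly by access to treatment.

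**Working it through.** No arithmetic applies. The check is one of logic: set the statements side by side and classify patients by ability and willingness.

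**Scope.** Sections 1.0 and 3.0 speak of frame-based SRS in general, which section 2.0 treats as wider than Gamma Knife ("frame-based SRS in a single fraction with Gamma Knife, Cyber Knife or linac-based treatment delivery"). Item 7 is narrower: Gamma Knife, at two named sites. Section 7.0 concerns the same treatment at the same two sites. The comparison between item 7 and section 7.0 is therefore like with like, and the conflict cannot be put down to a difference in scope. Below, "able" and "willing" refer to Gamma Knife SRS at those two sites.

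**Rule.** Let U be the patients who are unable and N those who are unwilling.

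- Target population: U or N.
- Removed by item 7: everyone not in N.
- Remaining: (U or N) and N = N.
- Lost from the target: U and not N, that is, unable but willing.

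**Classification.**

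| Patient | Sections 1.0, 3.0, 7.0 | Item 7 | Agreement |
|---|---|---|---|
| Able and willing | Outside the target | Excluded | Yes |
| Able, unwilling | In the target | Not excluded | Yes |
| Unable, unwilling | In the target | Not excluded | Yes |
| Unable, willing | In the target, offered enrolment | Excluded | **No** |

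Three of the four combinations agree. Only the last conflicts.

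**Size.** The protocol does not say how many patients are unable, how many are unwilling, or how far the two overlap. As a share of the target population, the conflicting group could lie anywhere from 0% to 100% on the information given.

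**The case against.** The strongest answer is that section 7.0 shows how item 7 is meant to work. Referral is offered first, and item 7 removes patients who take it up. The intent to admit both groups is stated three times, the treating radiation oncologist obtains consent under section 7.0, and in ordinary use a patient's willingness to have treatment at a site may be taken to imply being able to go there. This is good evidence of intent, and it makes item 7 look like a drafting slip and not a deliberate restriction. It does not remove the conflict. All three population statements list ability and willingness separately, and the list makes any single criterion disqualifying. Nothing in section 7.0 says that it overrides the list.

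A second objection limits the reach of the point, and it stands. Item 7 turns on willingness to be treated at the two named sites. A patient who will not make the journey because of travel, time or expense is not willing to be treated there and remains eligible. So does a patient who declines the head frame. A reader might infer that item 7 defeats the access rationale in section 2.0 outright, or that it bars anyone willing to have any form of frame-based SRS. The text supports neither.

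A reader might also infer that SRS candidacy is missing from the entry rules because no numbered item requires it. It is stated at the head of section 3.0, under which both lists fall, and section 7.0 makes a recommendation for Gamma Knife SRS the starting point for offering enrolment. Repeating it as a numbered item would be a drafting preference.

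**Conclusion.** The contradiction is real but narrow. Read literally, item 7 makes ineligible those patients who would accept Gamma Knife at the main campus or The Woodlands but cannot have it. Sections 1.0 and 3.0 place them in the target population, and section 7.0 offers them enrolment. Patients who are unwilling are unaffected, whether or not they are also unable.

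The size is unknown. Because two groups are named, a reader might infer that half of the target population is lost. The two overlap and the protocol gives no proportions, so that does not follow. Nor can an assumed share of referrals be multiplied by the 35 planned patients to count wrong refusals: patients refused at screening are never among the 35, since section 6.2 enrols to 35 evaluable patients.

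The wording changes no endpoint, hypothesis, stopping boundary, sample size or analysis, and the protocol gives no basis for saying that local control would differ between the two groups. The consequence is inconsistent screening and avoidable eligibility deviations. The conclusion rests on reading item 7 as written, with willingness not taken to include ability. It should be corrected because it is an operative enrolment rule and correction is cheap.

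**What to change.** Reconcile item 7 of the Ineligibility list with sections 1.0, 3.0 and 7.0. One way is to limit the exclusion to patients who are both able and willing to be treated with frame-based Gamma Knife SRS at the two named sites, so that it becomes the exact complement of the population that section 7.0 invites to enrol.

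Optionally, record at enrolment whether the patient was unable, unwilling or both. The baseline data listed in section 4.0 do not include this, and it would let the report describe who was actually enrolled.

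The cost is a one-line amendment and, if the option is taken, one REDCap field. No patients, visits or procedures are added.

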### **4.0 Research Plan and Methods**

The study utilizes a two-stage design with an inherent interim analysis after the first stage to stop the study early for futility. In the first stage of the study, the first 20 evaluable (defined as patients who complete the 6 month follow up) patients (See study design below) will be analyzed prior to making a decision to continue to the second stage of the study. Study data will be collected and managed using REDCap (Research Electronic Data Capture) electronic data capture tools hosted at MD Anderson. REDCap ([www.project-redcap.org](http://www.project-redcap.org)) is a secure, web-based application with controlled access designed to support data capture for research studies, providing: 1) an intuitive interface for validated data entry; 2) audit trails for tracking data manipulation and export procedures; 3) automated export procedures for seamless downloads to common statistical packages; and 4) procedures for importing data from external sources. In the case of multi-center studies REDCap uses Data Access Groups (DAGs) to ensure that personnel at each institution are blinded to the data from other institutions. REDCap (<https://redcap.mdanderson.org>) is hosted on a secure server by MD Anderson Cancer Center's Department of Research Information Systems & Technology Services. REDCap has undergone a

Governance Risk & Compliance Assessment (May 2014) by MD Anderson's Information Security Office and found to be compliant with HIPAA, Texas Administrative Codes 202-203, University of Texas Policy 165, federal regulations outlined in 21CFR Part 11, and UTMDACC Institutional Policy #ADM0335.

Those having access to the data include the study PI and research team personnel. Users are authenticated against MDACC's Active Directory system. External collaborators are given access to the database once approved by the PI, with their access expiring in 6 months but renewable in 6 months increments at the request of the PI. The application is accessed through Secure Socket Layer (SSL). All protected health information (PHI) will be removed from the data when it is exported from REDCap for analysis. All dates for a given patient will be shifted by a randomly generated number between 0 and 364, thus preserving the distance between dates. Dates for each patient will be shifted by a different randomly generated number. Following publication study data will be archived in REDCap. Since study data may be useful for future research studies performed under separate IRB approved protocols, study data will be archived indefinitely in REDCap. Since REDCap is a secure electronic database with controlled access, and because patient identifiers may be needed to link study data to data from other sources under future IRB approved protocols, patient identifying information will be retained in the archived database.

Initial data collection will include for each individual patient: baseline patient demographics, histology, Karnofsky performance status (6), presence or absence of systemic metastatic disease outside the brain, controlled or uncontrolled primary cancer, number of brain metastases, size and volume of largest brain metastasis treated as well as total volume of brain disease treated, dose prescribed and dose delivered to each brain lesion, and steroid use.

Patients will be followed every three months with history, clinical examination and brain MRI for 1 year. Follow up data collection at each follow-up visit will include the following:

1. Central nervous system toxicity such as Central nervous system necrosis, based on the CTCAE version 4.0.
2. Local failure in the brain on follow-up MRI defined as follows :
  - A. At least 20% increase in sum longest distance relative to lesion size prior to radiation treatment (reference 7 describes the RANO group criteria which is slightly different and uses nadir size rather than size prior to radiation)
3. Distant failure in the brain defined as additional new brain metastatic lesion(s) outside the irradiated region.
4. Overall survival.

If new lesion(s) are identified during follow up, the patient will be considered for FFSRT on protocol at the discretion of the treating physician. These new lesions are also followed every 3 months for 1 year with MRI and are considered for local control (LC) at the 6 month time point.

## 5.0 Treatment Planning Guidelines

All patients treated on this prospective study will be treated with FFRST with consistent setup, contrast-based CT simulation, MRI-fused contouring of tumor and normal tissue structures, and with standard dose prescriptions based on size of tumor and MD Anderson CNS Radiation stereotactic treatment planning guidelines for normal tissue tolerances.

All patients will be simulated supine in a CT-simulator with an aquaplast mask, bite block, and head holder. IV contrast will be required. Image acquisition will be at 1.0-mm slice thickness. A volumetric brain MRI will be obtained to be fused with the CT images obtained for treatment planning. A volumetric gadolinium-enhanced brain MRI is performed with 1.0-mm slice thickness to optimize disease extent, volume and aid in fusion with the CT simulation image set. If a volumetric brain MRI is not available, then comparable high-quality MRI with contrast enhancement obtained within 5 days of the CT simulation may be deemed acceptable for fusion by the treating physician.

The volumetric brain MRI will be fused with the CT simulation image set for optimal tumor localization and the tumor contoured on the CT data set. The gross lesion will be defined as the gross tumor volume (GTV). A 2 mm volumetric expansion will be placed on the GTV to create the planning target volume (PTV).

The following will be the dose prescription to the PTV based on maximum diameter of each individual brain lesion:

1. < 3.0 cm: 27 Gy/3 fractions
2. 3.0 - 3.9 cm: 30 Gy/5 fractions
3. 4.0- 5.0 cm: 25 Gy/5 fractions

Treatment planning will be performed with three-dimensional, intensity-modulated radiation therapy (IMRT) or volumetric modulated arc therapy (VMAT) techniques. Normal tissue (brain stem, optic nerves, optic chiasm, brainstem) constraints of dose are the following:

For **3 fraction** cases brain stem, optic nerves, optic chiasm, and brainstem, maximum point dose should not exceed 16 Gy in patients with no previous brain radiation, and 1 cc should not receive over 12 Gy.

For **5 fraction** cases brain stem, optic nerves, optic chiasm, and brainstem, maximum point dose should not exceed 22 Gy in patients with no previous brain radiation and 1 cc should not receive 20 Gy. Optimally the chiasm and optic nerve point dose should be kept less than 18 Gy and <0.02cc should receive less than 16.5 Gy but for tumors adjacent to the chiasm or optic nerve the former constraints are acceptable.

For all cases, mean brain dose should not exceed 8 Gy.

Treatment delivery will require the following quality assurance measures prior to each fraction of treatment:

1. Presence of radiation physicist, radiation oncologist and radiation therapist at the treatment console.

2. kV orthogonal imaging prior to cone-beam CT (CBCT) to confirm gross alignment of the patient's head and isocenter placement as compared to orthogonal digitally reconstructed radiographs (DRRs) generated from the treatment plan.
3. Non-contrast CBCT with appropriate isocenter shifts directed by the radiation oncologist to confirm match of metastatic target lesion seen on real-time cone-beam CT with planning CT contour of GTV. If the metastatic target lesion is unable to be seen on the non-contrast CBCT, then alignment of normal tissue brain structures near the metastatic target lesion will be necessary instead, such as bony skull and ventricles.
4. MV orthogonal imaging after CBCT and just prior to treatment delivery to confirm isocenter placement as compared to DRRs.

